**V2 (Month 3 ± 1 month): Injection visit 2**
At this visit, both groups will receive a tablet and headphones to listen to music during the botulinum toxin injections. The musical intervention, as described below, will begin immediately after the medical consultation and completion of the STAI-Y1 anxiety questionnaire. The CRA or nurse will set up the patient on the medical bed and place the Polar H10 chest strap. The patient, with or without assistance, will choose the preferred music. During a resting period of at least 10 minutes, the patient will listen to the selected music. The music duration can be adjusted to match the length of the medical procedure.

At the end of the injections (both groups), a Visual Analog Scale (0 to 10) will be used to assess perceived pain. The nurse or CRA will ask the patient to rate their satisfaction with the intervention via VAS. Anxiety will be quantified using the STAI-Y1 questionnaire. Time perception will again be assessed via self-report.

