# STUDY METHODOLOGY

## Evaluation criteria

### Primary endpoint

Patient stress, assessed during Injection Visit #1, will be estimated by changes in Heart Rate Variability (HRV), measured before and during the botulinum toxin injection session using the LF/HF ratio.

The LF/HF ratio is a reliable indicator of the balance between sympathetic and parasympathetic nervous system activity. It provides insight into stress regulation, cardiovascular health, and physiological adaptation. A lower LF/HF ratio may be associated with improved recovery, better emotional regulation, and a healthier autonomic nervous system balance.

HRV will be measured using a Polar H10 heart rate monitor belt. Data will be exported to the Elite HRV application and analyzed using KUBIOS software.

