### Secondary endpoints

- Patient stress during Injection Visit #2, estimated by changes in HRV, measured before and during the botulinum toxin injection session using the LF/HF ratio.
- Pain intensity experienced by the patient during Injection Visits #1 and #2, measured immediately after the injection session using a simple Numerical Rating Scale (NRS) ranging from 0 (“no pain”) to 10 (“worst imaginable pain”).
- Anxiety variation measured by the self-administered State-Trait Anxiety Inventory - Form Y, State subscale (STAI-Y1) during Injection Visits #1 and #2, before and after the botulinum toxin injections. The STAI-Y1 consists of 20 items rated on a 4-point Likert scale, from 1 (“Not at all”) to 4 (“Very much”) (see ANNEX 2).
- Patient’s perception of the duration of the session relative to the actual injection time during Injection Visits #1 and #2. This self-reported data will be collected at the end of each session.
- Patient satisfaction with the intervention assessed using a Visual Analog Scale (VAS) ranging from 0 (“no satisfaction”) to 10 (“highest satisfaction”), measured after the injections during Visits #1 and #2.
- Quality of the botulinum toxin injection conditions, as assessed by the physician immediately after each session during Visits #1 and #2, using a simple Numerical Rating Scale (NRS) from 0 (“extremely poor conditions”) to 10 (“extremely good conditions”).

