**V1 (Month 0): Injection visit 1 (inclusion visit)**
At this visit, informed consent will be obtained from the patient or their legal guardian. The physician will provide a copy of the signed consent form to the patient or their legal representative/trustee/designated person. The following data will be collected: age, sex, pathology, and date of first botulinum toxin injection. Once this information is recorded, randomization will be performed by the Clinical Research Associate (CRA) of the department.
For all injections, the same standardized protocol will be applied for each patient (ultrasound-guided or electromyography localization technique, MYOBOT needle [26G], analgesia by ice for palmar or plantar injections upon patient request) in an outpatient setting.

During the first injection visit, a Polar H10 heart rate monitor chest strap will be placed on the patient to measure stress induced by the medical procedure. A minimum recording period of 10 minutes is required prior to the injections to collect reliable baseline data. During this time, the physician will prepare the syringes for botulinum toxin injection. The patient will complete the self-administered anxiety questionnaire (STAI-Y1).

The control group (CT-IM) will not receive any specific intervention other than the Polar H10 heart rate monitor. This group will undergo botulinum toxin injections according to usual practice within the department, with the same evaluations as the intervention group (IM-IM).

The intervention group (IM-IM) will receive a tablet and headphones to listen to music during the botulinum toxin injections. Before the injection, during the waiting time, the patient, with or without assistance, will choose the music to listen to based on personal preferences. The music duration can be adjusted to fit the length of the medical procedure.

At the end of the injection session (both groups), a Visual Analog Scale (VAS) will be presented to the patient to rate pain on a scale from 0 to 10. The nurse or CRA will ask the patient to rate their satisfaction with the intervention using a VAS. Anxiety will be measured using the STAI-Y1 questionnaire. Time perception will also be evaluated based on patient self-report and compared to the actual duration of the medical procedure.

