## Dosage, administration modalities and duration

The headphones will be worn before and throughout the entire duration of the medical procedure. The patient must remain on the examination table for the entire duration of the measurements.

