## Product presentation

A pair of headphones and a tablet will be available for the entire duration of the study. The headphones will be placed on the patient’s ears once they are positioned on the examination table. The nurse assisting the physician during the botulinum toxin injections will help the patient select the music they wish to listen to. Additionally, the patient may navigate through the application to modify the music style or adjust the duration of the listening session, if desired. The objective is to ensure that the listening duration extends throughout the medical procedure, continuing until the completion of the injections. The listening session may also be controlled by the investigator or the nurse, who can stop the device at any time.

[figure not shown]

**Figure 3** : Application MUSIC CARE^®^

The MUSIC CARE® application is available for download on various platforms (AppleStore or PlayStore). The PMR department will have an account to allow patients to benefit from this therapeutic approach. The first image in Figure 2 shows the different session choices based on the patient’s preferences. In the context of the MUSIBOT study, the application will be used with the aim of reducing stress related to the medical procedure. A diagram is then presented to explain to the patient the "U-shaped" sequence. Once the patient selects the "pain" program, another page appears, allowing the patient to choose the music style they wish to listen to during the session. Music can be selected by category. The patient selects the music to listen to and is then asked to rate their current level of pain using a Visual Analog Scale (VAS). The music begins according to the "U-shaped" sequence, with a minimum duration of 20 minutes. The duration can be adjusted based on the length of the medical procedure. The patient/nurse controls the application and can modify settings as needed.

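### The protocol does not keep the 'before' HRV recording free of music: clearly at visit 2, and conditionally at visit 1, where sections 7.1 and 8.2–8.3 conflict

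*Protocol*

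**What the plan says.** **Endpoints.** Section 6.1.1 defines the primary endpoint as the change in HRV at visit 1, "measured before and during the botulinum toxin injection session using the LF/HF ratio". Section 6.1.2 carries the same construction to visit 2: "Patient stress during Injection Visit #2, estimated by changes in HRV, measured before and during the botulinum toxin injection session using the LF/HF ratio".

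**Visit 1 (section 7.1).** The arm is known before any HRV is recorded: "Once this information is recorded, randomization will be performed by the Clinical Research Associate (CRA) of the department". The strap is then placed, and "A minimum recording period of 10 minutes is required prior to the injections to collect reliable baseline data". The music arm "will receive a tablet and headphones to listen to music during the botulinum toxin injections. Before the injection, during the waiting time, the patient" chooses what to listen to. On this text, listening belongs to the injections and only the choice of music belongs to the waiting time.

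**Visit 2 (section 7.1).** The intervention is to start straight after the consultation and the STAI-Y1. The patient is set up with the strap, music is chosen, and then: "During a resting period of at least 10 minutes, the patient will listen to the selected music". No other pre-injection period is described.

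**Intervention (sections 8.2 and 8.3).** "The headphones will be worn before and throughout the entire duration of the medical procedure". Section 8.3 has them put on "once they are positioned on the examination table", and section 8.2 keeps the patient on the table for as long as measurements last. Neither section separates visit 1 from visit 2.

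**The concern.** A before-to-during change measures the effect of music on the response to injection only if the 'before' value is untouched by music. If music is already acting in that window, the subtraction removes part of the effect under study.

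Two things are at stake. At visit 1, exposure of the baseline would be confined to one randomized arm, because allocation precedes the recording, and it would bear on the primary endpoint. At visit 2, the change score would have a different reference state from the visit 1 score, although section 10.4 models the change between the two visits. No analysis can recover a baseline that was recorded under music.

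**Working it through.** **1. The plan's own figure.** Inputs from section 10.1: difference 1.8, SD 2.3, two-sided 5%, power 90%. By the normal approximation, n per group = 2(1.960 + 1.282)² × 2.3² / 1.8² = 2 × 10.51 × 5.29 / 3.24 = 34.3, so 35. The stated 35 reproduces. The noncentral-t solution is 35.3, essentially the same.

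**2. Visit 2 sequence.** Consultation and STAI-Y1; patient placed on the bed with the strap; music chosen; at least 10 minutes' rest with music; injections. Music cannot play before it is chosen, so the strap is on before the music starts. But no recording period is described between strap and music. The protocol does not label the rest as the 'before' recording, yet it is the only candidate.

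**3. Visit 1 sequence under each reading.**

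| Text followed | Music arm, 'before' | Control arm, 'before' |
|---|---|---|
| Section 7.1 | choosing music, not listening | no tablet or music |
| Sections 8.2–8.3 | headphones on, music possibly playing | no tablet or music |

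**4. Effect on the primary contrast if music is playing.** Let B and D be the expected LF/HF before and during injections without music. Let music lower D by 1.8, and let an assumed share f of that amount already be present in the music arm's baseline.

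- Control change: D − B.
- Music-arm change: (D − 1.8) − (B − 1.8f).
- Difference between arms: −1.8(1 − f).

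Two-sample t-test power, SD 2.3, noncentrality = [1.8(1 − f)/2.3] × √(n/2):

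| f (assumed) | Difference | Noncentrality, n = 35 / 40 | Power, n = 35 / 40 |
|---|---|---|---|
| 0 | 1.80 | 3.27 / 3.50 | 90% / 93% |
| 0.25 | 1.35 | 2.46 / 2.63 | 68% / 74% |
| 0.5 | 0.90 | 1.64 / 1.75 | 36% / 41% |

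The protocol gives no value for f; the table shows sensitivity and is not an estimate.

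**5. Effect at visit 2.** Let g be the lowering of the resting value by music. Both arms then have baseline B − g, and g cancels in the visit 2 between-arm contrast when it is the same in both. Across visits it does not cancel within an arm. In CT-IM the visit 1 change is D − B and the visit 2 change is (D − 1.8) − (B − g), so the within-arm shift is −(1.8 − g) rather than −1.8. This holds whichever visit 1 text is followed, because controls have no music at visit 1. In IM-IM a shift of +g arises only if visit 1 followed section 7.1; if visit 1 followed sections 8.2–8.3 with music playing, both of its baselines carry music.

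**The case against.** The strongest reply is that section 7.1 is the visit-specific text. It puts listening during the injections and calls the visit 1 recording baseline data, so it should govern over the general description in section 8. Headphones on is not music on: in section 8.3 music begins only after a programme and style are chosen and pain is rated. This stands in part. A reader might infer that the primary endpoint definitely subtracts away some of the music effect; the document does not support that, because it depends on which text staff follow and on whether music is playing. What remains is that no step holds playback until the baseline is closed, and section 2.5 hopes for a relaxing sound environment before the injections, so early listening is a plausible practice.

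Other limits also stand.

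- **Visit 2 contrast.** A reader might infer that the visit 2 comparison between arms is biased, or that the two visits cannot be modelled together. Both arms follow the same visit 2 procedure, and section 10.2 calls the secondary analyses exploratory. It is the interpretation of the between-visit change that suffers.
- **Direction.** Attenuation presumes that music lowers resting LF/HF. That is the trial's premise, not an established fact. If the patient is only handling a tablet, the direction is unknown.
- **Power table.** The share f is assumed, and treating a resting effect as a fraction of 1.8 is a simplification. The 1.8 comes from a virtual-reality study whose baseline procedure is not described.
- **STAI-Y1.** A reader might infer that it is completed during the visit 1 recording. Its sentence follows the one on the recording period but gives no time of its own.
- **Missing figures.** Figure 1 and the general study diagram are not shown and may give timing. They would not remove the conflict in the text.

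**Conclusion.** The point holds as an unresolved protocol inconsistency that should be fixed. For visit 2 confidence is high: the only pre-injection rest described is spent listening, so no music-free baseline of adequate length is provided for. The consequence there is confined to interpreting the visit 1 to visit 2 change, mainly in CT-IM, in an exploratory analysis.

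For the primary endpoint confidence is medium. The protocol does not fix whether the music arm's visit 1 baseline is music-free. If it is not, the bias is differential and, under the trial's hypothesis, towards no effect. The loss could be nil or large depending on f, which is unknown. The sample size calculation is sound on its own inputs, and the five extra patients per group are justified in section 10.1 mainly by unusable data, with no allowance stated for such attenuation.

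**What to change.** Reconcile the visit 1 and visit 2 descriptions in section 7.1 with sections 8.2 and 8.3, so that one measurement sequence applies in both arms and at both visits:

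- place the strap, with the STAI-Y1 completed at the same point in the sequence each time;
- complete a 'before' recording of at least 10 minutes with no headphones, tablet or music, including no music selection;
- start music only once that recording is closed.

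Listening before the injections can still follow the recording if the sponsor wants it. Figure 1 and the general study diagram should be checked against the revised text.

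The cost is revised visit-flow wording and about 10 more minutes at visit 2. The sample size and the analysis model need no change on this account. The change has to be in place before patients are recorded, since the baseline cannot be repaired afterwards.

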**Musical intervention**
The MUSIC CARE® application is a receptive musical intervention where music is selected according to patients’ personal preferences from a range of styles available on a tablet. A single individual music session is administered during the consultation. Music is delivered through headphones, accompanied by an eye mask, in a quiet room conducive to relaxation. The standard musical sequence, lasting 20 to 60 minutes, is structured in phases designed to gradually induce a state of relaxation according to the "U sequence" method.

The "U-shaped" musical sequence involves a progressive decrease in musical tempo, orchestral intensity, frequency range, and volume (descending phase of the U). After reaching maximal relaxation (bottom of the U), the music gradually increases in intensity and stimulation (ascending phase), facilitating reawakening. All sequences, developed according to the "U sequence" method, are produced by MUSIC CARE® (Paris, France).

[figure not shown]

**Figure 2**: "U" shaped musical sequence

This approach, used in music therapy, aims to induce relaxation by guiding the patient through a gradual reduction of musical stimulation followed by a progressive reactivation. During the descending phase, musical elements such as rhythm, intensity, frequencies, and volume are progressively diminished, allowing the patient’s nervous system to calm. The lowest point corresponds to maximal relaxation and calmness. The subsequent ascending phase gently raises stimulation to prepare the patient to return to alertness.

The sequences can be personalized by selecting styles, tempos, and melodies that promote relaxation and wellbeing.

MUSIC CARE® is not conventional music therapy requiring a qualified music therapist but provides therapeutic use of music directed by the patient across various settings. Patients may select from a broad array of musical genres, including classical (piano, violin, flute, etc.), jazz (trumpet, saxophone, trombone, etc.), and world music (India, Andes, Africa, etc.). All musical compositions have been recorded in high-quality studios with professional musicians to meet the application’s rigorous clinical standards. These recordings are exclusively for use within the app to prevent prior recognition by patients and avoid memory or conditioning effects.

Thus, with its extensive music selection, MUSIC CARE® distinctly differs from other forms of therapeutic interventions.

## General logistical organization of the trial

The trial will be conducted within the PMR department of the Clermont-Ferrand University Hospital. The implementation of the musical intervention and its explanation will be coordinated by a nursing assistant (NA).

Patients will be provided with dedicated headphones and will be trained by the NA, who assists the physician during the procedure, to operate the tablet interface. The nursing assistant has been trained and is qualified to select an appropriate musical program based on the patient’s preferences (MUSIC CARE® Paris, France), if necessary.

## Biological sampling and analyses

No biological samples or laboratory analyses are planned in this study.

## Expected duration of participant involvement

Total duration of patient participation in the study: 4 months. The study end date will be reported to the competent authority and the ethics committee (French CPP) within 90 days. In case of premature termination of the study, this information will be communicated to the competent authority and the ethics committee within 15 days.

# STUDY INTERVENTION

## Description of the application

To offer a musical intervention to our patients, a tablet preloaded with the MUSIC CARE application and a set of headphones is provided. MUSIC CARE is a digital therapeutic application currently used for managing pain, stress, and sleep disorders, aiming to improve patients’ daily lives. The purpose of this application is to soothe the patient during the medical procedure. The patient is able to interact with their environment and manage the application according to their preferences.

## Dosage, administration modalities and duration

The headphones will be worn before and throughout the entire duration of the medical procedure. The patient must remain on the examination table for the entire duration of the measurements.

## Product presentation

A pair of headphones and a tablet will be available for the entire duration of the study. The headphones will be placed on the patient’s ears once they are positioned on the examination table. The nurse assisting the physician during the botulinum toxin injections will help the patient select the music they wish to listen to. Additionally, the patient may navigate through the application to modify the music style or adjust the duration of the listening session, if desired. The objective is to ensure that the listening duration extends throughout the medical procedure, continuing until the completion of the injections. The listening session may also be controlled by the investigator or the nurse, who can stop the device at any time.

[figure not shown]

**Figure 3** : Application MUSIC CARE^®^

The MUSIC CARE® application is available for download on various platforms (AppleStore or PlayStore). The PMR department will have an account to allow patients to benefit from this therapeutic approach. The first image in Figure 2 shows the different session choices based on the patient’s preferences. In the context of the MUSIBOT study, the application will be used with the aim of reducing stress related to the medical procedure. A diagram is then presented to explain to the patient the "U-shaped" sequence. Once the patient selects the "pain" program, another page appears, allowing the patient to choose the music style they wish to listen to during the session. Music can be selected by category. The patient selects the music to listen to and is then asked to rate their current level of pain using a Visual Analog Scale (VAS). The music begins according to the "U-shaped" sequence, with a minimum duration of 20 minutes. The duration can be adjusted based on the length of the medical procedure. The patient/nurse controls the application and can modify settings as needed.

## Dispensing and compliance

Non applicable

## Authorized and prohibited medications and treatments during the trial

No additional analgesic medication beyond the patient’s usual prescription will be allowed during the procedure. Medications that could interfere with heart rate variability during the study (such as beta-blockers, antiarrhythmics, anxiolytics, benzodiazepines, antihypertensives, and calcium channel blockers) are prohibited.

The use of ice for plantar injections is permitted only if it was used prior to the study.

# DATA COLLECTION

Data collected in the case report form will include the inclusion and exclusion criteria (see above), demographic data (age, sex), date of first injection, injected muscles, dose administered, and type of botulinum toxin used, clinical evaluation data, pain level measured by a visual analog scale (VAS), heart rate variability (HRV) parameters, anxiety measurements before and after injections, patient-reported perception of time (in minutes) during the procedure, actual duration of the medical procedure, patient satisfaction with the intervention, quality of the injection conditions as assessed by the physician immediately after the session, and any potential adverse events encountered.

Regarding heart rate variability data, the following parameters will be collected: Mean RR interval, Mean Heart Rate, SDNN (standard deviation of NN intervals), RMSSD (root mean square of successive differences), pNN50 (percentage of successive RR intervals differing by more than 50 ms), TINN (triangular interpolation of NN intervals), VLF (very low frequency), LF (low frequency), HF (high frequency), LF/HF ratio, SD1 and SD2.

